- [12] Echocardiogram: one examination within 7 days prior to randomization, 7 days prior to surgical resection and at the end-of-treatment visit, plus additional examinations for clinically significant electrocardiographic abnormalities during the study period.
- [13] Pregnancy test: For women of childbearing potential, a serum pregnancy test is used. Performed within 7 days prior to first dose, 1 week prior to surgery, 3-6 weeks after surgery, end of treatment/withdrawal from study, and at Visit 1 of the safety follow-up period.
- [14] Imaging: including chest CT, abdominal ultrasound; PET-CT testing and cranial magnetic resonance MRI (1.5T scanning + enhancement; cranial CT may be used instead if the patient has a contraindication to magnetic resonance testing) may be performed up to 60 days prior to the first use of the study medication; bone scans will be performed only when clinically indicated, and the bone scans must have been performed within 42 days prior to the first dose of medication.
- ✓ Screening cycle, tumor assessment can be up to 4 weeks prior to first use of study drug, and imaging results obtained prior to signing informed consent can be used for screening period tumor assessment as long as they meet RECIST 1.1 requirements.
  - ✓ Full imaging evaluation was performed after the 2nd cycle of dosing and within 7 days prior to surgery for lung cancer.
  - ✓ Subjects in whom no imaging progression is observed during safety follow-up and survival follow-up should continue to have imaging evaluations at the same frequency until disease progression or initiation of other antitumor therapy.
  - ✓ In addition to disease progression confirmed by imaging, subjects who end treatment for other reasons should also be imaged as often as possible at the frequency specified in the protocol until documented confirmation of disease progression, initiation of new antitumor therapy, or death.
- [15] Lung function assessment: Normal or mild to moderate abnormal lung function ( $VC\% > 60\%$ ,  $FEV1 > 1.2L$ ,  $FEV1\% > 40\%$ ,  $DLco > 40\%$ ) to tolerate radical lung cancer surgery; assessed within 14 days prior to the first dose of drug, and once within 7 days prior to lung cancer resection.
- [16] Pathologic evaluation: pathologic diagnosis and evaluation within 90 days prior to first dose and after lung cancer resection, respectively.

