##### Initial follow-up (1st and 2nd follow-up)

The first follow-up visit will take place in the hospital approximately one month after the completion of pre-surgical treatment, and it will occur before or on the day of the lumpectomy. Surgery is scheduled to be performed within 4-6 weeks after finishing pre-surgical treatment. Prior to surgery, a contrast-enhanced PET/CT or CT scan will be conducted, and the results of pulmonary function tests will be reassessed. A second follow-up visit will occur approximately two months after the first follow-up visit and after the patient has undergone surgery. Procedures performed and samples collected during the study drug administration may be repeated one or more times during these two follow-up visits. Following the initial follow-up visit and surgery, patients will receive adjuvant therapy with sintilimab for up to 13 cycles as part of their standard care.

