#### **4.6 Additional follow-up**

After surgery, patients will have additional follow-up visits approximately every three months, with the possibility of more frequent check-ins. These follow-up visits

can be conducted over the phone or in the hospital. Patients will receive evaluations every three months for a total of two years, followed by visits every six months thereafter. As part of the follow-up, patients will undergo a CT or MRI scan of the lesion site or areas of potential spread every three months for the first two years. This will continue every six months for the next three years and then annually for a total of five years, until tumor recurrence or death occurs.

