#### **4.7 Survival visit**

After surgery, follow-up visits will be conducted every three months for the first two years, followed by visits every six months for an additional three years. Follow-up care includes, but is not limited to, performing CT or MRI scans of the lesion site or areas of potential spread until tumor recurrence or death occurs. During follow-up, the following parameters will be closely monitored and recorded: time to disease progression, time of death (with options for telephone follow-up and record-keeping), and any other therapeutic agents or treatments administered.

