### 5.1.2 Other indicators

- Major pathologic response (MPR) rate, defined as the proportion of subjects with  $\leq 10\%$  surviving tumor cells in the resected primary tumor and all resected lymph nodes. For pathological assessments, primary lung tumors and lymph node specimens were staged using the AJCC criteria (8th edition). Residual viable tumor percentage in primary tumors was determined from routine hematoxylin and eosin-stained specimens. Tumors with  $\leq 10\%$  viable cells were classified as having MPR. Pathological downstaging was defined as a reduction in ypTNM stage post-treatment, with no new lesions or progression of existing lesions.

- Event-free survival (EFS), defined as the interval from enrolment to the

earliest occurrence of local progression resulting in inoperability; unresectable tumour, disease progression or recurrence according to RECIST version 1.1 as assessed by the investigator; or death from any cause. Progression-free survival was treated as censored on the date of the last validated tumor assessment for subjects in whom no tumor progression or death was observed.

- Overall survival (OS), defined as the time from study entry (i.e., after signing ICF) to death from any cause. Subjects who were alive at the time of last contact had their overall survival censored at the date of last contact.

- Patients underwent radiological evaluations by investigators according to RECIST version 1.1 at baseline, after two cycles of neoadjuvant therapy, prior to surgical resection, and every 4 cycles during adjuvant therapy until disease progression, intolerable toxicity, death, or withdrawal of consent. Complete and partial responses were confirmed radiologically at least 4 weeks later, while stable disease was confirmed at least 8 weeks after the initial assessment. The ORR was defined as the proportion of patients achieving either a complete or partial response. Patients were followed up by visits or phone calls every 12 weeks to determine survival status.

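### Flow chart note [14] ends tumour imaging at new antitumor therapy, against sections 4.6-4.7 and 5.1.2; progression after a switch is then lost to EFS, which is distorted in a direction the protocol cannot settle

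*Protocol*

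**What the plan says.** The protocol gives three sets of rules for when tumour imaging ends.

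- **Study Flow Chart, note [14].** Subjects without imaging progression in safety and survival follow-up "should continue to have imaging evaluations at the same frequency until disease progression or initiation of other antitumor therapy". The next bullet covers subjects who end treatment for reasons other than progression. They are to be imaged "until documented confirmation of disease progression, initiation of new antitumor therapy, or death".
- **Sections 4.6 and 4.7, both starting after surgery.** Section 4.6 has scans at lengthening intervals, "then annually for a total of five years, until tumor recurrence or death occurs". Section 4.7 describes "performing CT or MRI scans of the lesion site or areas of potential spread until tumor recurrence or death occurs". Neither names new therapy as a stop.
- **Section 5.1.2.** Radiological evaluation is "every 4 cycles during adjuvant therapy until disease progression, intolerable toxicity, death, or withdrawal of consent". New therapy is not on this list either.

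Section 5.1.2 also defines EFS. Besides inoperability and unresectable tumour, its events are "disease progression or recurrence according to RECIST version 1.1 as assessed by the investigator; or death from any cause". Subjects with neither progression nor death observed are "censored on the date of the last validated tumor assessment". That sentence speaks of progression-free survival, but it stands within the EFS definition and is read here as its censoring rule. Start of new therapy is neither an event nor a reason for censoring.

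The first part of follow-up under section 4.5 adds "adjuvant therapy with sintilimab for up to 13 cycles as part of their standard care" after surgery.

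**The concern.** The EFS definition needs progression to be looked for whatever treatment the patient later receives. Note [14] stops the search when that treatment changes. The protocol names two participating hospitals (section 3.4), and each could follow a different passage.

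The loss is permanent. If the scans are taken, progression after new therapy can be counted or censored as the analysis requires. If they are not taken, only the censored version remains, and the main EFS result rests on which passage a site happened to read. The trial has a single arm, so no control group shares the error.

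**Working it through.** **1. Rules side by side**

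| Place | Patients | Is new therapy a stop? |
|---|---|---|
| Note [14], first follow-up bullet | No imaging progression | Yes |
| Note [14], second follow-up bullet | Ended treatment for other reasons | Yes |
| 4.6, 4.7 | After surgery | No |
| 5.1.2 imaging rule | Neoadjuvant and adjuvant periods | No |
| 5.1.2 EFS definition | All | Neither event nor censoring reason |

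For operated patients the flow chart contradicts 4.6-4.7. For patients who never reach surgery, 4.6-4.7 schedule nothing, so there is no direct contradiction. The flow chart is then the main long-term rule, and it still falls short of what the EFS definition needs.

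**2. What happens to a switcher under the flow chart**

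Survival follow-up continues after imaging stops (note [20]), and death from any cause is an EFS event. A patient who starts new therapy without documented progression is therefore:

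- censored at the last scan before the switch, if alive at the data cut-off; or
- an event on the date of death, even if progression came earlier.

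Two errors pull in opposite directions. Unseen or late-dated progressions raise EFS. The second error lowers it: switchers who later die stay in the risk set until death, while surviving switchers leave it at the switch, so those who stay all have an event.

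**3. Size**

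The protocol states no EFS rate, so there is no figure to reproduce. All inputs here are assumptions: 24-month EFS of 70% without switching; 10% or 20% switching at month 4 without progression; post-switch hazard ratio (HR) 1, 2 or 3; mean survival after progression 12 or 24 months; follow-up 24-48 months.

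Baseline hazard: λ = -ln(0.70)/24 = 0.01486 per month.

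With complete imaging and a switching share f:

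EFS(24) = (1 - f) × 0.70 + f × exp[-λ(4 + 20 × HR)]

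- f = 0.10, HR 2: 0.63 + 0.10 × exp(-0.01486 × 44) = 68.2%
- f = 0.20, HR 2: 0.56 + 0.20 × exp(-0.01486 × 44) = 66.4%
- f = 0.20, HR 3: 0.56 + 0.20 × exp(-0.01486 × 64) = 63.7%
- HR 1, any f: 70.0%

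The flow-chart result was simulated by Kaplan-Meier with later deaths counted as 5.1.2 requires (1,000,000 patients per scenario, simulation error about 0.1 point). Differences from complete imaging, in points at 24 months, over the two post-progression survival values:

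| Switching | HR 1 | HR 2 | HR 3 |
|---|---|---|---|
| 10% | -0.7 to -0.4 | +0.4 to +1.0 | +1.2 to +2.0 |
| 20% | -1.6 to -0.9 | +0.7 to +1.9 | +2.2 to +3.9 |

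If deaths after the switch were ignored, flow-chart EFS would be about 70% throughout. The error would then be 70.0 - 68.2 = 1.8 points (10%, HR 2) to 70.0 - 63.7 = 6.3 points (20%, HR 3), and zero at HR 1. The protocol does not ignore those deaths, so these figures do not apply.

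**4. Other assumptions**

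A second simulation took scans every 3 months, 24-month EFS of 65% without new therapy, and 10-30% switching between months 3 and 15. It gave overstatement of about 0.5 to 5.5 points at HR 2-3 and understatement of about 0.3 to 4.4 points at HR 1 or 0.5. At 20% switching, EFS with complete imaging against flow-chart imaging was 59.1-59.5% against 62.1-62.8% at HR 3, and 66.6-66.8% against 63.6-64.2% at HR 0.5.

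**The case against.** The best reply is that this is a small wording conflict on a secondary endpoint. EFS has no hypothesis, threshold or comparator, and 45 patients give a wide interval: at 70%, 1.96 × √(0.70 × 0.30/45) is about 13 points either way, well above any error in the table. The pCR endpoint and the stage 1 rule are untouched. Many patients who miss surgery already have an EFS event, because inoperability, unresectable tumour and progression all count, and the radiotherapy routes in 3.6.1 and 3.6.2 follow progression. For operated patients, nothing in the protocol suggests that 10-20% would start other therapy before recurrence. All of this stands and limits the weight of the point. It does not remove the contradiction or bring back scans that were not taken.

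Three stronger readings are tempting, and the documents do not support them.

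- A reader might infer that EFS is certainly biased upward. That needs switchers to have a worse outlook. This is the usual expectation, but the protocol gives no data on it, and counted deaths reduce the upward error and can reverse it.
- A reader might infer that there is no bias if switchers have the same hazard. With deaths counted, EFS is then understated.
- A reader might infer that adjuvant sintilimab, described as standard care, stops imaging in most operated patients. Section 5.1.2 schedules imaging during adjuvant therapy, and sintilimab is one of the study drugs in note [22], so other or new antitumor therapy does not naturally include it. What remains is that the protocol never says so.

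**Conclusion.** The point holds as a conflict between imaging rules that leaves EFS exposed. Note [14] is alone in making new therapy a stop. Following it discards progression data that the EFS definition calls for.

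The effect is a distortion of uncertain sign. Under the 70% scenario, 24-month EFS is overstated by about 0.4-3.9 points at hazard ratios 2-3 and understated by about 0.4-1.6 points at hazard ratio 1. The switching rate, the switchers' hazard and survival after progression are all assumed. Overstatement is the more plausible direction, but it is not established. The point concerns a secondary endpoint and is worth correcting because the loss cannot be undone and the correction is cheap.

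**What to change.** 1. In note [14], remove the start of other or new antitumor therapy as an imaging stop from both follow-up bullets, and reconcile the note with 4.6, 4.7 and 5.1.2. Operated patients are then imaged to recurrence or death as 4.6-4.7 already schedule, and progression seen after new therapy counts in EFS as 5.1.2 defines it.
2. State whether the same rule covers patients who do not reach surgery.
3. State that adjuvant sintilimab is not other antitumor therapy for this purpose, in line with the adjuvant-period imaging in 5.1.2.

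For operated patients the cost is wording only. If the rule is extended to patients without surgery, it costs a few additional scans, since 4.6-4.7 do not schedule theirs. A sensitivity analysis censoring EFS at new therapy can be left to the SAP; complete imaging keeps it possible.

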## List of Abbreviations

| Abbreviations and full spelling                        | Definition       |
|--------------------------------------------------------|------------------|
| ADLs (activities of daily living)                      | 日常生活活动           |
| AE (Adverse Event)                                     | 不良事件             |
| ALT (Alanine Amiotransferase)                          | 丙氨酸氨基转移酶（谷丙转氨酶）  |
| ANC (Absolute Neutrophil Count)                        | 中性粒细胞计数          |
| APTT (Activated Partial Thromboplastin Time)           | 活化部分凝血活酶时间       |
| AST (Aspartate Aminotransferase)                       | 天冬氨酸氨基转移酶（谷草转氨酶） |
| BUN (Blood Urea Nitrogen)                              | 尿素氮              |
| Glu (Blood Glucose)                                    | 葡萄糖              |
| Cr (Creatinine)                                        | 肌酐               |
| CFDA (China Food and Drug Administration)              | 国家食品药品监督管理总局     |
| CR (Complete Response)                                 | 完全缓解             |
| CRF (Case Report Form)                                 | 病例报告表            |
| CT (Computed Tomography)                               | 计算机X 射线断层扫描      |
| CTCAE (Common Terminology Criteria for Adverse Events) | 不良事件通用术语标准       |
| CK-MB (Creatine Kinase Isoenzyme)                      | 肌酸激酶同工酶          |
| DBIL (Direct bilirubin)                                | 直接胆红素            |
| ECOG (Eastern Cooperative Oncology Group)              | 东部肿瘤协作组身体状况评分标准  |
| ECG (Electro Cardio Gram)                              | 心电图              |
| EFS (Event-free survival)                              | 无事件生存期           |
| FT3 (Free-Triiodothyronine)                            | 游离三碘甲状腺原氨酸       |
| FT4 (Free-Thyroxine)                                   | 游离甲状腺素           |
| GCP (Good Clinical Practice)                           | 药物临床试验质量管理规范     |
| Hb (Hemoglobin)                                        | 血红蛋白             |
| HBV (Hepatitis B Virus)                                | 乙型肝炎病毒           |
| HCV (Hepatitis C Virus)                                | 丙型肝炎病毒           |
| HR (Hazard Ratio)                                      | 风险比              |
| INR (International Normalized Ratio)                   | 国际标准化比率          |
| ICF (Informed Consent Form)                            | 知情同意书            |

|                                                           |              |
|-----------------------------------------------------------|--------------|
| IrAE (Immune-related adverse events)                      | 免疫相关性不良事件    |
| MRI (Magnetic Resonance Imaging)                          | 核磁共振         |
| MPR (major pathologic response)                           | 主要病理缓解       |
| MTD (Maximum Tolerated Dose)                              | 最大耐受剂量       |
| NSCLC (Non-small Cell Lung Cancer)                        | 非小细胞肺癌       |
| ORR (Objective Response Rate)                             | 客观缓解率        |
| PD (Progressive Disease)                                  | 疾病进展         |
| pCR (Pathological complete response)                      | 病理完全缓解       |
| PI (Principal Investigator)                               | 主要研究者        |
| PLT (Platelet Count)                                      | 血小板计数        |
| PR (Partial Response)                                     | 部分缓解         |
| PT (Prothrombin Time)                                     | 凝血酶原时间       |
| PET/CT (Positron emission tomography computed tomography) | 正电子发射计算机断层显像 |
| RBC (Red Blood Cell Count)                                | 红细胞          |
| RECIST (Response Evaluation Criteria in Solid Tumor)      | 实体瘤疗效评价标准    |
| RFS (Recurrence-free survival)                            | 无复发生存期       |
| SAE (Serious Adverse Event)                               | 严重不良事件       |
| SD (Stable Disease)                                       | 疾病稳定         |
| SCLC (Small cell lung cancer)                             | 小细胞肺癌        |
| TBIL (Total Bilirubin)                                    | 总胆红素         |
| TSH (Serum Thyroid-stimulating Hormone)                   | 血清促甲状腺激素     |
| TRAE (Treatment-related adverse event)                    | 治疗相关不良事件     |
| ULN (Upper Limit of Normal)                               | 正常值上限        |
| VEGF (vascular endothelial growth factor)                 | 血管内皮生长因子     |
| WBC (White Blood Cell Count)                              | 白细胞          |

---

# **1. Research background and rational for the study**

## **1.1 Research background**

### **1.1.1 Lung cancer and its neoadjuvant therapy**

The 2018 Global Cancer Incidence and Mortality Statistics report shows that there are 18.1 million new cancer cases worldwide, of which Asia accounts for nearly half, and of the 9.6 million cancer deaths, Asia accounts for nearly 70%. Lung cancer continues to be the first malignant tumor in terms of incidence (11.6%) and mortality (18.4%), which directly endangers human health. The most common cause of lung cancer is smoking, and lung cancer in never-smokers is more common in women in East Asia and is associated with environmental exposures, including secondhand smoke, pollution, carcinogens, and genetic factors. According to the analysis of lung cancer incidence and deaths in China in 2014, the incidence of lung cancer ranked 1st among malignant tumors in Chinese men and 2nd among malignant tumors in Chinese women, and about 75% of lung cancer patients were found to be in the middle or late stage, with a very low 5-year survival rate. Lung cancer is categorized into non-small cell lung cancer (NSCLC) and small cell lung cancer (SCLC) according to cell type, with NSCLC accounting for about 85% of the total number of lung cancer cases. NSCLC can be divided into three subtypes: adenocarcinoma (40%), squamous cell carcinoma (30%), and large cell carcinoma (15%), which is characterized by slower cell growth and division and later metastasis compared with small cell carcinoma.

Surgical treatment is the main treatment for early stage non-small cell lung cancer, and it is also the only treatment that can make lung cancer cured. It is suitable for stage I-II lung cancer, stage IIIa lung cancer, and partially selective stage IIIb lung cancer whose tumor is confined to one side of the chest cavity. Unfortunately, however, some of the patients with NSCLC in China are in advanced stages when they are found and have missed the best opportunity for surgical treatment. Neoadjuvant therapy, also known as preoperative therapy, mainly refers to the pre-implementation of systemic cytotoxic drug therapy before providing treatment for patients with locally advanced malignant tumors. The standard treatment for patients with stage II disease is surgery followed by adjuvant platinum-based two-agent chemotherapy. Numerous trials and meta-analyses have shown that patients who receive 3-4 cycles of adjuvant

chemotherapy have only a 5% improvement in overall survival. Neoadjuvant therapy has been studied in patients with stage II NSCLC, and preoperative neoadjuvant therapy is usually better tolerated, allowing direct observation of drug efficacy, with no increase in postoperative morbidity or mortality, and an overall survival benefit similar to that of adjuvant therapy. The presence of tumors in mediastinal (N2) lymph nodes is a staging determinant in most stage IIIA patients. However, the time of documented N2 disease (preoperative vs. postoperative) and the extent of N2 disease determine the prognosis and treatment strategy of the patient. Patients with N2 disease have been found to have a worse prognosis when mediastinal lymph node enlargement is observed on CT of the chest and further mediastinal lymph node biopsy is performed, or PET/CT is performed for further evaluation. If these patients undergo direct surgery, the overall 5-year survival rate is 15%. As for neoadjuvant therapy (chemotherapy  $\pm$  radiotherapy), recent trials have demonstrated an overall 5-year survival rate of 25%. Neoadjuvant therapy followed by surgery for patients with preoperatively diagnosed N2 disease has become one of the standard therapeutic regimens in major clinical guidelines. Since the 1990s, the research syndrome of preoperative neoadjuvant chemotherapy has been increasing year by year, which aims to reduce the scope of the lesion, lower the stage of tumor, increase the rate of complete surgical resection, kill systemic microscopic metastatic foci, avoid recurrence and metastasis, and prolong the survival period. Preoperative neoadjuvant therapy followed by surgery is one of the treatment options for IIIA/N2 and IIIB NSCLC.

